### Allocation

Allocation to trial arms will be performed after recruitment, consent and baseline data collection by the statistician who will be blind to the contact centre identity.

Contamination

Whilst it is possible that staff may move between contact centres allocated to different trial arms, we anticipate that this will have little impact. We will, however, attempt to measure/evaluate the extent to which this occurs by our follow-up attempts of contact.

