## Study population

As this is a cluster RCT, contact centres rather than the staff employed in the contact centres (including managers, supervisors and call handlers) will be recruited. All staff will have the opportunity to participate in the intervention. For the evaluation components, staff will have the option of taking part on an opt-in basis.

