## Randomisation

Randomisation will occur in month three. The unit of randomisation is contact centres. A computer-generated block randomisation algorithm will be used to randomly allocate each contact centre to start the intervention at one of five time points, three months apart. Randomisation in this way allows us to introduce the intervention to each site in an unbiased way unrelated to time or the particular circumstances of each site. It also helps ensure there is approximate balance on average across all the intervention start times in terms of participant or contact centre characteristics.

Steps to minimise bias

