### Data collection timepoints

In order to minimise cost and participant burden for this trial, and since the main purpose of the trial is to test study processes and procedures, data will only be collected at a maximum of three occasions per site: at the end of the control period, and at 3 and 6 months after the end of the intervention in each site. Sites 1 and 6 will not have a control period, and sites 5 and 10 will not have a post-intervention period, in order to minimise the duration of the study for which there is no concurrent vertical comparison between control and post-intervention periods. To increase the response rate, participants will be paid a small amount (£5 end of control period and £10 for 3 months data) for taking part in data collection.

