### Assessment of unanticipated outcomes

We will provide each contact centre with a sheet to record harms such as injuries as a result of using the equipment. The contact centre staff will be made aware of this and be asked to record any harms they think are a result of the intervention. We will ask them to detail the type of activity where the harm occurred, the type of harm (e.g. injury) and the date and time. We will collate this data from all contact centre every three months. We will also use the focus groups as a way of eliciting any unintended consequences.  Adverse events will also be a standing item on all Study Management and Study Steering Committee meetings.

Control/comparator group

Waiting list control – all 10 sites will receive no intervention for between 3 and 12 months after study set-up is complete; then they will receive the intervention.

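### Allocation is said to follow baseline data collection, but the schedule puts every outcome measurement after allocation; the stated 3-to-12-month wait for all ten sites cannot hold five starts three months apart

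*Protocol*

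**What the plan says.** The Allocation paragraph, under Steps to minimise bias, states: "Allocation to trial arms will be performed after recruitment, consent and baseline data collection", carried out "by the statistician who will be blind to the contact centre identity".

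The Randomisation section says "Randomisation will occur in month three" and that a computer algorithm will "randomly allocate each contact centre to start the intervention at one of five time points, three months apart".

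Data collection timepoints caps assessments at three for any one centre: "at the end of the control period, and at 3 and 6 months after the end of the intervention in each site". It adds: "Sites 1 and 6 will not have a control period, and sites 5 and 10 will not have a post-intervention period".

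The Control/comparator group paragraph says "all 10 sites will receive no intervention for between 3 and 12 months after study set-up is complete", followed by the intervention.

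On individuals, Study population says: "For the evaluation components, staff will have the option of taking part on an opt-in basis". Recruitment aims for 27 people at each centre for each round of outcome data, 270 in total. Retention plans to record length of employment, and Table 2 counts leavers and new joiners, including among research participants.

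**The concern.** Measuring participants before allocation protects a cluster trial in two ways. Who is in the study cannot depend on the allocation, and the first measurement cannot be coloured by knowing it. The protocol claims this protection, yet its own timetable appears to put every measurement after the start dates have been drawn.

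Staff opt in individually and cannot be blind to a workplace programme. Keeping the statistician blind to centre identity protects the draw of start dates. It does not govern who volunteers at a centre afterwards. People who consent once a start date is known, or once activities are running, may differ from those who consented earlier.

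The primary-outcome interval feeds the first progression criterion. Aim 2 also asks whether recruitment procedures suit a confirmatory trial, so a safeguard that never operated could be carried forward as if it had been tested.

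**Working it through.** **Inputs.** Randomisation in month three, and five starts 3 months apart (Randomisation). Measurement occasions, and the sites lacking a control or post-intervention period (Data collection timepoints). Intervention of about 3 months (Duration of the intervention). Stated wait of 3 to 12 months for 10 sites (Control/comparator group).

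**Assumptions.** The lead L from randomisation to the first start is not given in the text, so 0 and 3 months are both tried. Set-up is taken as complete at randomisation. Sites are paired as k and k+5, which fits the pairs 1/6 and 5/10 that the protocol names.

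**Step 1: the stated wait.** Five starts span (5 − 1) × 3 = 12 months. The stated window is 12 − 3 = 9 months wide, which holds 9/3 + 1 = 4 starts, or 4 × 2 = 8 sites. The figure for all 10 sites is not reproduced. Moving the time origin does not help, because a 12-month span cannot fit a 9-month window.

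**Step 2: the timeline.** Wait for sequence k = L + 3(k − 1). The end-of-control measurement falls when the wait ends. Sites 1 and 6 have none, so their first measurement is 3 + 3 = 6 months after their start. Months are counted from randomisation.

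| Sites | Wait, L = 0 | Wait, L = 3 | End-of-control measurement (L = 0 / L = 3) | First measurement of any kind (L = 0 / L = 3) |
|---|---|---|---|---|
| 1, 6 | 0 | 3 | none | 6 / 9 |
| 2, 7 | 3 | 6 | 3 / 6 | 3 / 6 |
| 3, 8 | 6 | 9 | 6 / 9 | 6 / 9 |
| 4, 9 | 9 | 12 | 9 / 12 | 9 / 12 |
| 5, 10 | 12 | 15 | 12 / 15 | 12 / 15 |

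Waits run from 0 to 12 months or from 3 to 15 months.

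**Step 3: order of events.** The end of the control period is the allocated start, so its date is unknown until allocation. Of the 8 end-of-control site assessments, 0 can precede allocation. This does not depend on L or on Figure 1, which is not shown.

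**Step 4: could baseline mean something earlier?** Data collection timepoints schedules no earlier occasion. Design and methods links the baseline points to the supply of activPAL devices and gives the cost of collecting baseline data everywhere at once as a reason for the staggered design. The £5–10 vouchers for baseline and outcome assessments (Retention) match the £5 at the end of control and £10 at 3 months. The protocol's baseline is therefore the staggered end-of-control measurement.

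**Step 5: loss before first measurement if everyone consents at randomisation.** This bears on the remedy. With L = 0 and the protocol's turnover of 21% to 24% a year:
- Sites 2 and 7 (3 months): 1 − 0.79^0.25 = 5.7% to 1 − 0.76^0.25 = 6.6%.
- Sites 5 and 10 (12 months): 21% to 24%, or 27 × 0.21 = 5.7 to 27 × 0.24 = 6.5 people per site.

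**The case against.** The best defence is that these are two wording slips in a feasibility study. Cluster allocation is computer-generated by someone blind to centre identity, the primary outcome is measured by device, and the analysis is declared exploratory. All of that stands and limits the severity. It does not make the Allocation sentence true.

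A reader might go further in four ways that the documents do not support.

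- **That staff consent is shown to follow allocation.** The Allocation paragraph places consent before it, and nothing contradicts this for the initial participants. Since Study population speaks of recruiting centres rather than staff, recruitment and consent may even be meant at centre level, which is achievable by month three. Per-round, opt-in recruitment leaves the order unassured for later joiners. It does not disprove it.
- **That the protocol would leave later joining invisible.** Table 2 counts new joiners among research participants, Retention records length of employment, and Statistical analysis plans sensitivity analyses for staff turnover. What is missing is narrower: when each person consented relative to allocation.
- **That the share of later joiners can be calculated.** This would need a rule that numbers are topped up to 27 at each round. None is stated, and 270 in total equals 10 × 27, which fits a single cohort.
- **That sites 1 and 6 lacking a pre-intervention measurement is itself the error.** It is a disclosed design choice. The fault is only that the Allocation sentence does not reflect it.

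The phrase about no control period may also mean only that no control data are collected at sites 1 and 6, just as sites 5 and 10 receive the intervention but have no post-intervention measurement. That leaves open whether the true range is 0 to 12 or 3 to 15 months. It does not rescue 3 to 12.

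**Conclusion.** The point holds on the text alone. A listed step to minimise bias claims that baseline data precede allocation. This is met at 0 of the 8 sites with an end-of-control measurement, and the other 2 sites have no such measurement. Consent before allocation is stated but not assured for later joiners, and the items listed for collection would not show when they consented. The 3-to-12-month wait fits four of the five starts, whatever the lead.

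The size of any resulting bias cannot be derived from the protocol and is likely to be modest for this trial, for the reasons granted above. The first progression criterion is also only one of six. The main cost would fall on the confirmatory trial, if it inherited this safeguard as proven. The conclusion about order rests only on the single month-three randomisation and the listed measurement occasions. The exact waiting ranges rest on the assumed leads of 0 and 3 months.

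**What to change.** Keep the design and the measurement schedule.

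1. **Allocation:** delete the claim that allocation follows baseline data collection. State that randomisation in month three precedes all outcome measurement and is done by the statistician blind to centre identity.
2. **Consent:** where practicable, take staff consent and demographics at all ten centres before start dates are announced to them.
3. **Recording:** log each participant's consent date relative to that announcement and to the centre's intervention start. Report numbers and characteristics of those consenting before and after.
4. **Optional analysis:** an estimate restricted to early consenters may be added, but it should carry a caution. Loss before first measurement differs by allocated start (about 6–7% at sites 2 and 7 against 21–24% at sites 5 and 10, under the assumptions in the working), so it would compare differently selected groups.
5. **Control/comparator group:** restate the waiting range to match the start schedule in Figure 1. The text alone does not settle which range is right.

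The cost is two wording changes, one data field and one descriptive table. The earlier consent round is the only real burden, given two researchers and scattered sites, hence the qualification where practicable. No outcome assessment or activPAL wear is added. Later joiners cannot be prevented, only identified.

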## Sampling and sample size

All employees at a site are likely to take part in some or all of the intervention activities. However, employees will have the option of taking part in the research evaluation component. When we discuss the sample size, we are referring to the number of people taking part in the research evaluation (not those only taking part in intervention activities). The sample size and target difference are the same as another similar study that proposed a sample size of 160 per arm to detect a reduction in workplace sedentary behaviour of 45 minutes per day [49]. Since we will have 6 control and post-intervention cross-sectional comparisons (see **Figure 1**), the target sample size is 160/6=~27 per contact centre per data collection period. There are 10 contact centres so we aim to recruit at least 270 employees in total taking part in the research evaluation. An aim of this feasibility study is to test sample size assumptions and produce a more accurate sample size calculation for a future study.

# The Intervention

## Theoretical basis

The intervention is in part based on two main theories: Social Cognitive Theory [63] and the Social Ecological Model (SEM) [64]. The intervention also aims to create a sense of ownership to increase the likelihood of longer-term sustainability [65]. While the SCT addresses many personal determinants and socio-environmental factors, the SEM takes the proposed multifaceted approach one step further to consider not only the individual and interpersonal levels, but to also consider the intervention at the organisational, environmental, and group level and takes into account the interactions between each of these [66]. By targeting multiple levels of the workplace, Stand Up for Health will aim to foster an atmosphere that will create a social norm within the office community to be able to sit and stand within the workplace. The SEM justifies and predicts that Stand Up for Health’s multifaceted approach will be effective, acceptable, feasible and sustainable. We also take a systems based approach, by recognising that the implementation and sustainability of the intervention is dependent on how adaptive the control centre system is to change.

The causal factors of sedentary behaviour in the workplace are complex and numerous, therefore no single activity (e.g. standing desks, goal setting) is likely to create significant change on its own. This complex, theory-based, public health intervention has been developed using the 6SQuID framework [65] and addresses theories of change at the individual; social/cultural; environmental; and organisational levels. The intervention addresses the complex causal factors of sedentary behaviour by exploring the theories of change through a range of evidence-based activities (see **Table 1**). Whilst activities will vary depending on local context (e.g. office and work space set-up) there must be at least one activity from each theory of change included in the intervention.

As an adaptive intervention, the fidelity of the intervention is to the theories of change rather than being prescriptive about activities that catalyse change. To ensure transferability, it takes into account the specific system (the contact centre, how it organises its work and how SUH will fit into the system) and context (e.g. layout of the centre, work-time flexibility, budget and resources available). Additionally, it includes all employees from the start of development, with the aim of creating a social norm to be able to stand more at work. By gaining insight from contact centre staff about their specific needs, this approach is more likely to lead to a sustainable and effective intervention [65].

## Development of the intervention

The programme theory was developed through a comprehensive literature review and qualitative work in a pilot contact centre. The intervention was developed using the six steps in quality intervention development (6SQuID) framework [65].

### 6SQuID Step 1: Defining and understanding the problem and its causes

Evidence on the causes of sedentary behaviour in the workplace, and existing sedentary behaviour interventions in contact centres and other workplace were identified through comprehensive literature reviews and surveys in the pilot contact centre.

### 6SQuID Step 2: Identifying which factors can be modified

Based on reviews of the evidence-base and qualitative data collection, all factors leading to sedentary behaviour in the contact centre were identified to ascertain which of these were potentially modifiable. Modifiable factors with the greatest scope for change were considered in order to identify which specific factors should be targeted through intervention activities.  These are described in the Fishbone Diagram  (**Figure 2**).

### 6SQuID Step 3: Deciding on the mechanism of change (theory of change)

These factors were used to develop the programme theory (**Figure 3**) and underlying theories of change below (**Table 1**).

### 6SQuiD Step 4: Clarifying how the mechanisms of change will be delivered (theory of action)

During this phase a workshop was held at the test contact centre to introduce staff to examples of intervention activities and equipment for the workplace. The workshop activities were developed based on feedback from staff in the focus groups. Staff were asked to add to the list with their own ideas, and also prioritise the ones which they wanted to try out.  The research team fed back the results to the SUH implementation group that then decided the final intervention activities to be implemented. There was at least one activity from each theory of change and they took account the resources, the assets (e.g. local spaces, existing equipment, spare spaces)  and budget available. Once the specific intervention activities were chosen the team worked with the contact centres to decide on an action plan for delivery and implementation of the activities (who, what, when, where).

### 6SQuID Step 5: Testing and adapting the intervention

Contact centre staff will be assisted and guided by the researchers during two wellness committee meeting to establish and set goals for the programme. Continuous feedback was gathered from staff throughout the duration of the intervention so that the delivery of activities can be adapted as necessary.

Results of the pilot

The pilot intervention is still being implemented and developed 18 months after it started. The contact centre has reported that 25% of staff now use standing desks (an increase from almost none). There are a number of different activities going on at any one time and the call centre staff are constantly thinking of new activities to implement. The contact centre also asked to ‘bolt on’ a mental health component - the research team worked with them to implement mindful activities which were either standing up interventions (e.g. jigsaw puzzles on a stand-up desk) or activities that encouraged them to leave their desk and be mindful (e.g. LEGO, knitting). This additional component is currently being implemented and has not yet been evaluated.

## The intervention to be delivered to contact centre staff

6SQUiD Stages 4 and 5 will form the basis of the tailored intervention for each contact centre. The hypothosised theories of change (Stage 3) remain constant but the theories of action are specific to each contact centre.  The initial stage of the intervention includes a ‘workshop’ that takes place at a contact centre, where staff have a chance to try out, suggest and vote for the activities they want to try out.  They also describe the environment, location, existing equipment and other assets which are then used to plan the activities. Some small pieces of equipment will be available to loan and try out through the SUH research team. Whilst the number of activities is not limited, there must be at least one activity from each theory of change. These activities are then converted into an action plan to be implemented over a number of weeks. A key intervention component is the creation of a SUH implementation group made up of all levels of contact centre staff who ensure that activities are implemented.  At the end of the intervention period a second workshop is held to check in as to which activities have worked and which haven’t. Further prioritisation and choosing of future activities is undertaken. All equipment and activities will be risk assessed, and details of how to use the equipment/undertake the activities provided. A website will be developed with useful resources, and opportunities for the contact centres to blog/share their experiences and create a community of SUH contact centres.

# Table 1.  Theories of change underpinning the intervention, and examples of activities

| **Theory of Change** | **Example of Activities*** |
| --- | --- |
| *Organisational* | SUH implementation group (made up of all levels of staff; this is the only obligatory activity); management led action plans; inclusion of non-sedentary behaviour as part of organisational strategies and goals; inclusion of non-sedentary behaviour activities for staff into roles and responsibilities (e.g. for supervisors); inclusion of ‘standing’ time into the working day. |
| *Environmental* | Equipment: Standing desks or a standing desk team area, bicycle desks, other equipment in communal places.  Repurposing or changing the environment: standing communal areas with mindful/enjoyable activities such as jigsaws or knitting, or a darts board; moving printers further away; exercise spaces; boards on walls to draw on. |
| *Social/cultural* | Group activities in work time such as five minutes of stretching per hour; group goal setting; exercise classes before or after shifts; competitions between workspaces or teams; workplace challenges; rewards for standing more/being more physically active; educational prompts. |
| *Individual behaviour* | Individual goal setting, active travel to and from work, lunchtime walks; apps; links to local groups and activities. |

*These are not exhaustive and the contact centre staff are encouraged to develop and think of their own activities.

### Duration of the intervention:

Duration of the intervention is defined as the period in which the centres take to develop their preferred activities for each theory of change, prepare an action plan for sustained engagement and test out some of the activities. This process is expected to take around three months, but may be dependent on the contact centre.

## Outcome measures

As this is a feasibility study we will be testing out the methods of collecting data on outcomes, as well as preliminary estimates of effectiveness. Table 2 outlines the methods/instruments used

# Table 2. Methods for Quantitative Data Collection

| **Outcomes** | **Measurement** |
| --- | --- |
| *Primary* |  |
| Sedentary time in workplace (objectively measured) | The activPAL™ is a small, thigh-worn device for assessing posture and is the preferred measurement instrument for assessing changes in occupational sitting [67, 68]. Participants wear the device continuously for seven days (during waking/sleeping hours and water-based activity) to provide adequate reliability [68, 69]. Following recommended procedures [69], we will isolate and determine changes in accumulated sedentary time whilst at work as our primary outcome. |
| *Secondary* |  |
| Sedentary time in workplace (subjectively measured) | The Occupational Sitting and Physical Activity Questionnaire (OSPAQ) will be used as a secondary measure given the favourable validity and reliability properties of this instrument [67, 68]. |
| Sedentary behaviour (overall) | The activPAL™ device to assess changes in:   - Prolonged sitting time in the workplace (bouts of ≥ 30 minutes) - Total sedentary time (i.e. including time outside the workplace such as at home and leisure time); workplace & total standing time; workplace & total sit-to-stand transitions |
| Physical activity | Physical activity will be assessed using both objective and subjective instruments.  Objective: activPAL™ device to assess changes over time in workplace and total stepping (utilising the stepping variable derived from the activPAL™ monitor)  Subjective: The International Physical Activity Questionnaire (long), last 7 days self-administered [68] will be used to quantity time spent in different domains of physical activity. This validated and reliable instrument assesses occupational, transportation, housework and recreation/leisure-time physical activity. |
| Productivity | Objective measures of productivity may include: absenteeism, presenteeism, call handling time, time spent talking, time spent on hold, time spent wrapping up a call, attendance, or sick leave. Subjective measures will be assessed using the Utrecht Work Engagement Scale and other measures in similar studies [69-70]. |
| Mental wellbeing | Warwick-Edinburgh Mental Well-being scale (WEMWBS) [71] |
| Musculoskeletal  health | Roland-Morris Disability Questionnaire: validated 24 item tool to measure back pain [72] |
| Activities | Questionnaires developed by the researchers to measure use and preference. |
| Staff turnover | Number of people leaving and number of new joiners over the study period (both in the contact centre as a whole and in the people taking part in the research) |

We will also collect data on demographics (age, gender, medical conditions which may impact on sedentary behaviour), activities use and preference; staff turnover.

